#### Statistical analysis

SPSS and Excel will be used to perform the statistical analysis. A probability (p) of less than 0.05 will be considered to be significant. Data will be presented for all arms of the study group. Data will be expressed as means ± standard deviation and proportions or rates. The analysis will be by intention to treat.

Descriptive analysis will be used to describe the primary and secondary outcome variables and to compare these outcome variables among the treatment arms of the two RCTs. Comparisons between the two arms of the randomised group will be done by applying Chi/square testing to crude rates of cumulative implantation and ongoing pregnancy and by using life table analysis to account for the factor of time to implantation or pregnancy. The relative contribution of predictive factors of success in any of the treatment arms, such as female age and duration of subfertility will be assessed by univariate and multivariate logistic regression and Cox regression.

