## Methods

### Study design

The OPTIMIST trial is a nationwide multicentre RCT. The cohort will consist of 1,500 women screened for ovarian reserve by an AFC prior to IVF or intracytoplasmic sperm injection (ICSI) treatment. Two RCTs are embedded in this cohort. Based on the AFC, women will be classified into four categories; AFC less than 8 (predicted poor responders), AFC 8-10 (predicted low-normal responders), AFC 11-15 (predicted normal responders) or AFC above 15 (predicted hyperresponders). RCT 1 will contain 300 women with an AFC below 11; RCT 2 will contain 300 women with an AFC of more than 15. A total of 25 academic and non-academic centres in the Netherlands will participate. An economic analysis is incorporated to assess the cost-effectiveness of an ORT and subsequent individualised FSH dosage in IVF or ICSI treatment. Inclusion was started in May 2011. This study will be conducted in accordance with the principles of the Declaration of Helsinki and in accordance with Good Clinical Practice. The study protocol has been approved by the Institutional Review Board (IRB) of the University Medical Center Utrecht (MEC 10-273) and by the board of directors of all participating centres.

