### Recruitment, consent and randomisation

Eligible women with an indication for a first IVF or ICSI treatment cycle or a first IVF or ICSI treatment cycle after birth of a child will receive oral and written information from their attending physician. The investigator will explain the study fully and in sufficient detail to allow the women to make an informed decision whether to participate or not. If a woman is willing to participate, written informed consent will be obtained. Based on AFC classification women will be entered into one of the four AFC classes (see Figure 1). Participants, excluding the predicted normal responders, will be randomly allocated to a standard or individualised FSH regime. All predicted normal responders will receive the standard dosage. Randomisation will be performed centrally by a web-based randomisation program and will be stratified by centre.

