### Study population

All subfertile women indicated for a first IVF or ICSI cycle, who are aged < 44 years, have a regular menstrual cycle and no major uterine or ovarian abnormalities at TVS are considered to be eligible for participation. Women with polycystic ovary syndrome (PCOS) and (uncorrected) endocrine or metabolic abnormalities, as well as women undergoing IVF after oocyte donation, will not be included.

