#### Outcome measures

The primary study outcome is the cumulative pregnancy rate achieved within 18 months after randomisation resulting in live birth. Pregnancies can be obtained in treatment cycles with fresh embryos as well as in subsequent cryo/thaw cycles. Spontaneous pregnancies between treatment cycles will also be taken into account.

The data will be integrated in a cost-effectiveness analysis. Differentiation will be made between direct medical costs (all health care sector costs), direct non-medical costs (costs outside the health care sector that are affected by health status or health care) and indirect costs of the fertility treatment (costs of sick leave due to fertility treatment). For medical costs, the process of care will be divided into two cost stages (cost of fertility treatment, cost of pregnancy), which can reoccur if women have repeat treatment cycles within the study period. These costs will be computed from the period of inclusion to the end of follow-up (18 months).

Direct non-medical and indirect costs may be generated if women are absent from paid work, either for visiting the fertility clinic during IVF or ICSI treatment or due to sick leave associated with physical or psychological side-effects of this treatment. The Health and Labour Questionnaire [13] will be used to document absence from paid work.

Fertility health care utilisation consists of hospital visits, TVS, gonadotrophins, endocrine laboratory tests, ovum pick-up, IVF or ICSI laboratory work and hospital care. Volumes of health care resource use will be measured alongside the clinical study in several participating centres by using a checklist.

Secondary study outcomes consist of the number of retrieved oocytes, the occurrence of poor response or hyperresponse, OHSS grade 2/3, the rate of cycle cancellation, the number of multiple pregnancies and total IU of FSH used per stimulation cycle.

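### The arms are compared on crude rates and an unadjusted life table, although centre is a randomisation stratum and predictive factors are named: a modest, avoidable loss of precision

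*Protocol article*

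**What the plan says.** All references are to the protocol article.

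- **Arm comparison (Statistical analysis).** "Comparisons between the two arms of the randomised group will be done by applying Chi/square testing to crude rates". The rates named are those of implantation and ongoing pregnancy. The sentence goes on to add a second approach, "by using life table analysis to account for the factor of time to implantation or pregnancy". Neither approach is given strata or covariates.
- **Regression (same section).** Logistic and Cox models are planned, univariate and multivariate. Their stated object is "The relative contribution of predictive factors of success in any of the treatment arms, such as female age and duration of subfertility". They are not described as a way to estimate an adjusted treatment effect.
- **Randomisation (Recruitment, consent and randomisation).** "Randomisation will be performed centrally by a web-based randomisation program and will be stratified by centre". Under Study design: "A total of 25 academic and non-academic centres in the Netherlands will participate".
- **Outcome (Outcome measures).** "The primary study outcome is the cumulative pregnancy rate achieved within 18 months after randomisation resulting in live birth". The chi-square sentence does not name this outcome, and it does not call the chi-square the primary analysis.
- **Age range (Study population).** Women are eligible "who are aged < 44 years, have a regular menstrual cycle".

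**The concern.** A comparison of two proportions that ignores known predictors leaves their share of the outcome variance in the error term. Here the protocol names two such predictors itself, admits women up to 43 years, and already plans regression models containing them, yet the treatment comparison makes no use of them. Nor does it use centre, the one variable on which randomisation is stratified.

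What is at stake is power. RCT 1 was sized for 80% with almost nothing to spare, so a gain that needs no extra women is worth taking. Fixing the adjustment set before outcomes are seen also removes a later choice between crude and adjusted results.

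**Working it through.** **Inputs.** From Sample size calculation: RCT 1, 25% vs 40%, 300 couples; both RCTs, 30% vs 41%, 600 women; RCT 2, 35% vs 42%, 300 women, stated power 24%; two-sided alpha 0.05, power 80%. Assumed: 1:1 allocation, as no ratio is stated; R², the share of outcome variance explained by covariates, as no prognostic strength is given.

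**Step 1: reproduce the plan (uncorrected chi-square).**

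n per arm = [1.960·√(2·p̄·(1−p̄)) + 0.842·√(p₁(1−p₁) + p₂(1−p₂))]² / (p₂−p₁)²

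For RCT 1, p̄ = 0.325:
- 1.960·√0.43875 = 1.298
- 0.842·√0.4275 = 0.550
- n = (1.298 + 0.550)² / 0.15² = 151.9, so 152 per arm, 304 in total (stated 300)

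Power with 150 per arm = Φ[(0.15·√150 − 1.298) / 0.654] = Φ(0.824) = 79.5%.

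The same method gives 592 for the combined comparison (stated 600; power at 600 is 80.5%) and 23.7% for RCT 2 (stated 24%). With a continuity correction the totals would be 330 and 628, so the trial was sized for the uncorrected, unadjusted test.

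**Step 2: allow for covariates.** Adjustment acts approximately like a larger sample: effective n = n / (1 − R²). For RCT 1 at R² = 5%: 150 / 0.95 = 157.9, and Φ[(0.15·√157.9 − 1.298) / 0.654] = Φ(0.897) = 81.5%.

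| Assumed R² | RCT 1 power | Combined power | Total needed for 80% in RCT 1 |
|---|---|---|---|
| 0 | 79.5% | 80.5% | 304 |
| 3% | 80.7% | 81.7% | 296 (2 × 152 × 0.97, rounded up per arm) |
| 5% | 81.5% | 82.5% | 290 |
| 10% | 83.6% | 84.5% | 274 |

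RCT 2 rises only from 23.7% to 25.8% at R² = 10%.

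**Step 3: simulation check.** 2,000 runs per scenario, 25 centres, permuted blocks of 4 within centre, one baseline covariate. Assumed log odds ratios per SD of the covariate were 0.3, 0.5 and 0.8, with centre SDs on the logit scale of 0.2, 0.3 and 0.3. The adjusted model contained the covariate but not centre; the centre-stratified test was Cochran-Mantel-Haenszel.

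| Comparison | Crude chi-square | Covariate-adjusted logistic |
|---|---|---|
| RCT 1 | 79.5%, 78.5%, 78.8% | 80.8%, 80.8%, 83.5% |
| Combined | 81.0%, 80.9%, 81.1% | 82.0%, 82.9%, 86.4% |

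The gain is about 1 to 5 points. Stratifying by centre alone changed power by at most about 1 point, and not always upward. With equal rates in both arms, the crude test rejected in 4.6% to 5.8% of runs, including a scenario with no covariate or centre effect.

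**Step 4: RCT as a stratum in a combined comparison.** On the plan's own rates, RCT explains 0.05² / (0.30 × 0.70) = 1.2% of the variance in controls and 0.01² / (0.41 × 0.59) = 0.04% in the experimental arm, about 0.6% on average. That is worth 0.2 to 0.3 points of power.

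**The case against.** The strongest reply is that nothing is broken. A crude chi-square is valid after centre-stratified randomisation, its simulated type I error stays near 5%, and chance imbalance in age is ordinary sampling error that its standard error already covers. The size of the gain rests wholly on an assumed R², at the low end it is about 1 point, and 300 against 304 women is rounding. All of this stands, and it limits the point to efficiency.

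Several stronger readings are tempting but not supported:

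- **That ignoring centre seriously inflates the standard error.** The direction is right in theory, but at the centre effects assumed the consequence was negligible.
- **That strong prognostic factors are being wasted.** The article names predictive factors but gives no strength. For AFC class, the Background says that reserve tests predict ovarian response and not pregnancy. The sample-size section does assume different control rates in the two RCTs, but offers nothing for AFC class within RCT 1.
- **That the primary analysis is a crude chi-square.** The test carries no such label, its sentence names implantation and ongoing pregnancy, and a life table stands beside it.
- **That a pooled test is planned without strata.** Pooling appears in the sample-size reasoning; the analysis section describes no pooled test.

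A last reply is that a condensed article leaves covariates and the handling of centre to the analysis plan. An adjusted analysis may indeed be specified there, so its absence from the trial cannot be asserted. But the article does not stay silent: it states a crude comparison and gives regression another purpose. That stated choice can fairly be questioned.

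**Conclusion.** The point holds as a missed gain in precision. The stated arm comparison is unadjusted, while the protocol stratifies randomisation by centre and plans models containing its own named predictive factors for a different purpose. In RCT 1 the gain is from 79.5% to about 81% to 84% power, provided that covariates explain 3% to 10% of outcome variance; that range is an assumption. The gain would come from female age and duration of subfertility, with centre contributing almost nothing.

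A reader might infer that the crude results would be biased or the test invalid. Neither the documents nor the calculations support that. Nor would adjustment repair the low power that the protocol itself reports for RCT 2.

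**What to change.** In the Statistical analysis section, or in the analysis plan before outcome data are examined:

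- For cumulative pregnancy leading to live birth within 18 months, pre-specify in each RCT a treatment-effect model adjusted for female age, duration of subfertility and centre. With 300 / 25 = 12 women per centre per RCT on average, enter centre as a random effect or group the small centres.
- Allow AFC class as an optional covariate in RCT 1, decided in advance.
- Report a marginal risk difference with 95% CI, so that the result stays on the scale used to size the trial.
- Stratify any combined 600-woman comparison by RCT.
- Keep the crude chi-square as a supportive analysis.

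The cost is wording. Age and centre are needed for eligibility and randomisation, AFC for classification, and the planned predictor models already require age and duration. Leave the randomisation strata unchanged: inclusion began in May 2011, so altering them would be a mid-trial change, and splitting RCT 1 by AFC class would leave about 6 women per centre and class if the classes were equal in size.

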**Methods/Design:**

Multicentre RCT in subfertile women indicated for a first IVF or intracytoplasmic sperm injection cycle, who are aged < 44 years, have a regular menstrual cycle and no major abnormalities at transvaginal sonography. Women with polycystic ovary syndrome, endocrine or metabolic abnormalities and women undergoing IVF with oocyte donation, will not be included. Ovarian reserve will be assessed by measuring the antral follicle count. Women with a predicted poor response or hyperresponse will be randomised for a standard versus an individualised FSH regime (150 IU/day, 225-450 IU/day and 100 IU/day, respectively). Participants will undergo a maximum of three stimulation cycles during maximally 18 months. The primary study outcome is the cumulative ongoing pregnancy rate resulting in live birth achieved within 18 months after randomisation. Secondary outcomes are parameters for ovarian response, multiple pregnancies, number of cycles needed per live birth, total IU of FSH per stimulation cycle, and costs. All data will be analysed according to the intention-to-treat principle. Cost-effectiveness analysis will be performed to assess whether the health and associated economic benefits of individualised treatment of subfertile women outweigh the additional costs of an ORT.

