The key question in the economic evaluation is to assess whether the health and associated economic benefits of individualised treatment of subfertile women in terms of increased ongoing pregnancy rates and reduced rates of hyperstimulation, outweigh the additional costs of an ORT. The economic evaluation will be designed as a cost-effectiveness analysis with the costs per pregnancy resulting in live birth within 18 months as the primary outcome measure. Cost-effectiveness of each strategy will therefore be expressed as costs per live birth. The incremental cost-effectiveness ratio (ICER) of each individualised dose-adjustment strategy as compared to a strategy with standard FSH dose will be estimated as the ratio between difference in costs between strategies and the difference in pregnancy rates, and reflects the extra costs required to obtain one additional live birth. If in the predicted poor response group individualised FSH treatment following an ORT increases the live birth rate without affecting OHSS rates, individualised treatment is the dominant strategy. If in the predicted hyperresponse group individualised FSH treatment following an ORT reduces the rate of OHSS, without affecting live birth rates, individualised treatment is the dominant strategy.

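### The named between-arm tests are attached to implantation and ongoing pregnancy, not to the primary outcome of pregnancy within 18 months resulting in live birth

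*Protocol article*

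**What the plan says.** The Outcome measures section states: "The primary study outcome is the cumulative pregnancy rate achieved within 18 months after randomisation resulting in live birth". The abstract (Methods/Design) gives nearly the same definition: "The primary study outcome is the cumulative ongoing pregnancy rate resulting in live birth achieved within 18 months after randomisation". The Sample size calculation starts from an expected gain in pregnancies resulting in live birth and takes 25% versus 40% for RCT 1.

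The Statistical analysis section has two sentences on comparing arms. The first is general and covers both RCTs: "Descriptive analysis will be used to describe the primary and secondary outcome variables and to compare these outcome variables among the treatment arms". The second names the methods for the comparison. One is "applying Chi/square testing to crude rates of cumulative implantation and ongoing pregnancy". The other method, which brings in timing, is "using life table analysis to account for the factor of time to implantation or pregnancy".

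The secondary list opens with "Secondary study outcomes consist of the number of retrieved oocytes, the occurrence of poor response or hyperresponse, OHSS grade 2/3" and goes on to cycle cancellation, multiple pregnancies and FSH use. Neither implantation nor ongoing pregnancy as a separate endpoint is in it.

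The Economic analysis section sets "costs per pregnancy resulting in live birth within 18 months as the primary outcome measure". It then describes the denominator of the incremental ratio as "the difference in pregnancy rates, and reflects the extra costs required to obtain one additional live birth".

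**The concern.** A confirmatory test should be run on the endpoint that was defined and powered. Here the methods are named for other events: implantation, ongoing pregnancy and, in the life table, pregnancy without further qualification. All of these come before live birth.

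An analyst following the text literally would have two chi-square results, on implantation and on ongoing pregnancy, judged against one threshold of p < 0.05. Neither is marked as confirmatory and neither is the stated primary outcome. If losses between implantation and birth differed between the dose arms, a conclusion drawn on the earlier events need not carry over to live birth.

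The cost-effectiveness ratio has a milder form of the same problem. Its denominator is worded as a pregnancy difference while the ratio is read as a cost per live birth.

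**Working it through.** **1. The plan's own power figures.** Inputs are from the Sample size calculation: two-sided alpha 0.05, 300 women per RCT, 600 in both together. Equal allocation is assumed. With n per arm and p̄ the mean of the two rates,

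power = Φ{ [ |p2 − p1| − 1.96·√(2p̄(1 − p̄)/n) ] / √( [p1(1 − p1) + p2(1 − p2)]/n ) }.

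- RCT 1, 25% v 40%, n = 150: (0.15 − 1.96 × 0.05408)/0.05339 = 0.824, power 79.5%. The formula for 80% power gives 304 in total with pooled variance and 300 with unpooled variance. The stated 300 reproduces.
- Both RCTs, 30% v 41%, n = 300: (0.11 − 1.96 × 0.03907)/0.03881 = 0.861, power 80.5%. The stated 600 reproduces.
- RCT 2, 35% v 42%, n = 150: (0.07 − 1.96 × 0.05619)/0.05604 = −0.716, power 23.7%. The stated 24% reproduces.

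These calculations are sound. The section introduces its rates as pregnancies resulting in live birth, so the stated power already refers to the primary outcome.

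**2. Endpoint by endpoint.**

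| Place in the article | Event |
|---|---|
| Abstract, primary outcome | Ongoing pregnancy resulting in live birth, 18 months |
| Sample size calculation | Pregnancy resulting in live birth |
| Outcome measures, primary | Pregnancy within 18 months resulting in live birth |
| Statistical analysis, descriptive sentence | Primary and secondary outcomes; no test named |
| Statistical analysis, chi-square | Cumulative implantation; ongoing pregnancy |
| Statistical analysis, life table | Time to implantation or pregnancy |

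The logistic and Cox regressions named at the end of that section are for predictive factors such as age and duration of subfertility, not for the comparison of arms. So no named between-arm test carries the live-birth qualifier. Implantation is in neither the abstract's outcome list nor the one in Outcome measures.

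**3. Size of the wording gap in the cost-effectiveness ratio.** Let ΔC be the cost difference, ΔP the difference in ongoing pregnancy rates, and L the share of ongoing pregnancies lost before live birth, taken as equal in both arms. The document gives no value for L. The live-birth difference is then (1 − L)·ΔP, and

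(cost per extra live birth)/(cost per extra ongoing pregnancy) = [ΔC/((1 − L)ΔP)]/[ΔC/ΔP] = 1/(1 − L).

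- L = 2%: 1/0.98 = 1.02
- L = 5%: 1/0.95 = 1.05
- L = 10%: 1/0.90 = 1.11

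**The case against.** The best defence is that this is shorthand. The abstract's own phrase for the primary outcome contains the words ongoing pregnancy, so the chi-square sentence may simply have dropped the live-birth qualifier. That is possible for ongoing pregnancy, although the article does not say so. It cannot be true of implantation. It is also fair that the preceding sentence promises a comparison of the primary outcome between arms. The primary outcome is therefore not left out, but that sentence speaks of descriptive analysis and names no test.

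The shorthand defence is stronger for the cost-effectiveness ratio. The Economic analysis section otherwise speaks of live birth, including in its measure of cost-effectiveness and in both dominance statements. The Sample size calculation likewise opens with pregnancies resulting in live birth and then says only pregnancy rate. The ratio therefore needs clarification; the text does not show that its denominator is wrong.

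One could also say that a fuller protocol or analysis plan would settle the matter. It might, but the difficulty is not an omission. The article positively names endpoints for its tests, and they differ from its primary outcome.

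Two stronger readings are tempting and are not supported.

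- A reader might infer that power for live birth is below the stated 80%. Setting 25% against 38% or 37%, for example, gives 68% or 61%. But the rates in the sample size are already live-birth rates, and that calculation shrinks only the treated arm. Even if 25% and 40% were ongoing pregnancy rates, an equal 2–10% loss in both arms would give 78.3% to 73.1%.
- A reader might infer that implantation would be counted per embryo, so that the unit is not the randomised woman. The article defines no unit. Cumulative implantation and time to implantation are compatible with a first event per woman.

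**Conclusion.** The point holds as an inconsistency between the Statistical analysis section and the rest of the article. The named chi-square and life-table analyses are not attached to the defined primary outcome, and one of the tested events, implantation, is not an outcome of the trial at all. This rests on the text alone and needs no outside figure.

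The sample size and its stated 80% power stand. The factor of 1.02–1.11 for the cost-effectiveness ratio is an illustration only. It applies if the denominator were really ongoing pregnancy and if losses were equal across arms; unequal losses could move it either way. The document does not establish that the ratio would in fact be computed that way.

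**What to change.** In the Statistical analysis section:

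- Make the confirmatory chi-square, in each RCT, the comparison of the proportion of randomised women with a pregnancy conceived within 18 months of randomisation that results in live birth.
- Run the life table on time from randomisation to that pregnancy.
- List implantation and ongoing pregnancy as secondary outcomes, counted per randomised woman.

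In the Economic analysis section, state that the denominator of the incremental ratio is the between-strategy difference in the same live-birth rate.

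The cost is a few sentences of wording, with no change to sample size or design. The primary outcome as defined already requires the outcome of each pregnancy conceived in the 18 months. The article describes cost follow-up only to 18 months, so the sponsor should confirm that births after that point are recorded.
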